### iSupport: online self-help training and support program

iSupport consists of information, skills training, and support for caregivers, using problem-solving and cognitive-behavioral therapy techniques, addressing the needs of caregivers (Fig. 3). The online program contains the following five themes: (1) what is dementia? (one lesson); (2) being a caregiver (four lessons); (3) caring for me (three lessons); (4) providing everyday care (five lessons); and (5) dealing with challenging behavior (ten lessons).

Each lesson presents a topic and is comprised of several interactive exercises rather than long pages with theoretical information only. Caregivers are given instant feedback when they provide their answers to the questions in the exercises. Caregivers can compose their own personalized education plan for which they can select any lesson they decide would be particularly pertinent. Figure 3 provides an overview of the lessons, summarizing the themes. An adapted version to the Indian context of the generic WHO field-testing version of Support was pilot tested for usability and acceptability by potential caregivers in India (*N* = 10). We will monitor adherence using the online support tool including time spent on the tool, per week. Internal to the support system are positive messages at the completion of lessons included to increase adherence.

**Fig. 3 Fig3:**
[figure not shown]
iSupport: online self-help training and support program

### Comparison condition: education-only control

The comparison condition – education-only – is an e-book based on a brochure created for caregivers of people with dementia by Alzheimer’s Disease International in collaboration with the World Health Organization [34]. It contains information on the following topics: basic information about dementia; living with and caring for a person with dementia; practical tips on managing dementia; personal and emotional stress of caring; caring for yourself; help for you, the carer, and; what support tools are available through Alzheimer’s Disease International. It does not have an interactive component like iSupport to teach caregivers skills for managing their mood or techniques for coping with challenging behaviors in people living with dementia.

### Sample size calculation

Sample size calculation is guided by the primary outcome change in burden (ZBS) at 6 months after baseline. Alpha (two-tailed) was set at 0.05 power at 80%. A standardized effect size of .33 – a relevant effect for the Zarit Burden Scale (ZBS) [35] – was calculated using earlier findings from a recent trial which evaluates power/sample size for these studies [36]. Using Stata 12, minimum sample size for each group was identified as 80. To take account of study dropout we increase this number by 30% (*N* = 208; 104 per group).

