## Methods and analyses

The trial design is a two-group RCT to establish the effectiveness of an online self-help training and support program (iSupport) compared to an education-only comparison condition (EOC) which provides education about dementia and caregiving through an on-line e-book (Fig. 1). The objective is to examine the effect of this online self-help training and support program on depression and anxiety outcomes. The RCT will last 6 months in total, including pre measurement (T0), first follow up (T1, 3 months after T0) and second follow-up (T2, 3 months after T1). The timeline of assessments and measures are described in Fig. 2.

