### Randomization

After screening, participants who fulfil the inclusion criteria are requested to provide informed consent to enrol in the study. Next, they are asked to fill out the questionnaires at baseline, after which randomization is carried out using an automated computer-generated random number allocation, stratified by sex and relationship to the care recipient (spouse/other) with a block size of 2. Participants are masked to their intervention status.

To randomize the participants, a table is filled with “real random” 0 or 1 codes preceding the start of the project, drawn with equal probability (50%) from the Random.org site [33]. This table is subsequently linked to the table with the accumulation of participant data. Immediately before randomization, the questionnaire script determines what block-condition (male/female; spouse/no spouse) applies to the participant. Next, with a block size of 2, there are two options:If a new block must be opened for the new participant: the participant’s condition will be determined by the “real random” value in the linked table. Thus, if the random value is 0, the participant’s condition will be 0 and if the random value is 1, the condition will be 1If a block is already open and partially filled (thus, with a block size of 2, with one other respondent), the new participant’s condition will be the other condition of the first participant. So, if the first participant has condition 0, the new participant’s condition will be 1, etc.

Baseline characteristics of individuals randomized to either of the two conditions will be compared to ensure that randomization was successful. If an individual that is enrolled in the trial drops out after enrollment, is lost to follow-up or discontinued from the study, their data will be analyzed using the intention-to-treat principle.

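### The stated inputs give about 145 participants per group, not 80; 80 per group has about 55% power for an effect of 0.33 SD

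*Protocol article*

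**What the plan says.** All the inputs are in the Sample size calculation section of the protocol article, except the design and the allocation ratio.

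- Sizing outcome: "Sample size calculation is guided by the primary outcome change in burden (ZBS) at 6 months after baseline".
- Error rates: "Alpha (two-tailed) was set at 0.05 power at 80" per cent.
- Effect: "A standardized effect size of .33", described as relevant for the ZBS and derived from an earlier trial.
- Result: "Using Stata 12, minimum sample size for each group was identified as 80".
- Dropout: "To take account of study dropout we increase this number by 30" per cent, which gives 104 per group and N = 208.

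The Methods and analyses section describes a parallel two-group comparison: "The trial design is a two-group RCT to establish the effectiveness of an online self-help training and support program (iSupport"). The Randomization section gives 1:1 allocation, with codes "drawn with equal probability (50%) from the Random.org site". No baseline-to-follow-up correlation, covariate adjustment or repeated-measures gain is mentioned in connection with the sample size.

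**The concern.** The section prints outcome, sidedness, alpha, power, effect size, software and result, so the result can be checked. An effect of one third of a standard deviation normally needs well over 100 per group for 80% power in a two-arm comparison, so 80 looked far too small. If the printed figure is wrong, the 80% power claim does not describe the trial as written. A non-significant burden result could then be read as evidence against an effect the sponsor calls relevant, when the trial had only about an even chance of detecting it.

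**Working it through.** **Inputs.** Effect d = 0.33, two-sided alpha 0.05 (z = 1.960), power 80% (z = 0.842), all from Sample size calculation. Two groups from Methods and analyses; 1:1 allocation from Randomization.

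**1. Attempt to reproduce 80.**

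n per group = 2(1.960 + 0.842)² / 0.33² = 144.1, so 145. The noncentral t calculation gives 145.1, so 146. The stated 80 is not reproduced, and the gap is far beyond rounding or software differences.

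**2. Power at the sizes the plan gives (d = 0.33, two-sided 0.05, unadjusted).**

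| Analysed per group | Normal approximation | t-based |
|---|---|---|
| 80 | 55.1% | 54.6% |
| 104 (no dropout) | 66.3% | 65.9% |

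For 80 per group by the normal approximation: 0.33 × √(80/2) = 2.087; 2.087 − 1.960 = 0.127; Φ(0.127) = 0.55. Set to 55% power instead of 80%, the two-sample formula returns exactly 80.

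**3. Effect detectable with 80% power at 80 per group.** (1.960 + 0.842) × √(2/80) = 0.443 (t-based 0.446), so about 0.45 SD.

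**4. Other standard calculations.**

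| Variant | n per group |
|---|---|
| One-sided alpha 0.05 | 114 (t-based 115) |
| One-sample or paired formula | 73 (t-based 75) |
| Two-sided alpha 0.05/3, for three primary outcomes | 193 |
| Two-sided alpha 0.20 | 83 |

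None gives 80. The one-sided and alpha 0.20 variants contradict the stated alpha, and the paired formula is not a between-group comparison.

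**5. Unstated baseline correlation.** Suppose 0.33 is in units of the raw ZBS score SD and r is the correlation between baseline and 6 months.

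- ANCOVA: n = 144.1(1 − r²). Setting n = 80 gives r = √(1 − 80/144.1) = 0.667.
- Change score: n = 144.1 × 2(1 − r). Setting n = 80 gives r = 1 − 80/(2 × 144.1) = 0.72.

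The protocol gives no r, so the range below is an assumption (normal approximation):

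| r | n, ANCOVA | n, change score | Power at 80 per group, ANCOVA | Power at 80 per group, change score |
|---|---|---|---|---|
| 0.5 | 109 | 145 | 67.4% | 55.1% |
| 0.6 | 93 | 116 | 74.2% | 64.6% |
| 0.7 | 74 | 87 | 83.2% | 76.9% |
| 0.8 | 52 | 58 | 93.6% | 91.0% |

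**6. Dropout step.** 80 × 1.30 = 104 is computed as worded. It leaves 80 per group only if dropout is at most 1 − 1/1.30 = 23.1%. If 30% dropout was meant, 104 × 0.70 = 72.8, so about 73 remain, with t-based power of 50.8% at d = 0.33. Keeping 80 after 30% dropout would need 80/0.70 = 114.3, so 115 per group.

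**The case against.** The strongest reply is that the original calculation used a baseline correlation that the article left out. The effect is called relevant for the ZBS, which could mean 0.33 of the score SD tested on change. In that case r of about 0.67 to 0.72 gives 80. Such values are not implausible: Table 1 quotes an intra-class correlation of 0.88 to 0.89 for the scale. The planned regression and GEE models also add confounders, and the full protocol may hold the Stata inputs.

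Part of this stands. The 55% is the power of an unadjusted comparison with 0.33 scaled to the SD of the analysed variable. It is not necessarily the power the trial will have. The text does not exclude the other scaling, and the source of the effect size is not at hand.

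It does not rescue the printed figure, for three reasons.

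- The sizing outcome is itself change in burden. On the direct reading 0.33 is already the standardized effect on change, and 145 applies.
- The Table 1 coefficient is a reliability figure with no stated interval. Used as r = 0.88 it would give 144.1(1 − 0.88²) = 32.5, so 33 (ANCOVA), or 144.1 × 2 × 0.12 = 34.6, so 35 (change score). It does not explain 80 either.
- The Statistical analyses section names paired t tests, regression for possible confounders, and GEE with an arm indicator. Baseline ZBS is not among the variables listed under Covariates or as confounders in Table 1. The precision gain that 80 would rely on is therefore not secured by the stated analysis.

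The objection on dropout is also fair in part. The text says only that the number is raised by 30%, and that multiplication is correct. The figures for 73 per group apply only if 30% dropout was intended.

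Finally, the Discussion describes the study as a first attempt to show feasibility and potential, which softens the stakes. The Methods section, however, sets out to establish effectiveness.

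**Conclusion.** The statement is wrong as written. The printed inputs require 145 to 146 analysed per group. At 80 per group they give about 55% power, and about 66% if all 104 are analysed; 80% power at 80 per group corresponds to about 0.45 SD. These figures assume a two-sample comparison, equal group sizes, and 0.33 in units of the SD of the variable analysed. If 0.33 is in raw-score SD units and baseline is adjusted for, ANCOVA power at 80 per group runs from 67% (r = 0.5) to 94% (r = 0.8). The 80% claim then depends on a correlation the protocol does not give. That the figure cannot be reproduced is certain; the trial's actual power depends on what the original calculation assumed. The dropout point is secondary and conditional.

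**What to change.** Keep N = 208; the Trial status section says enrolment is under way. First retrieve and report the inputs of the original Stata calculation, including the scale of the 0.33 and any correlation used. Then do one of the following.

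- **(a)** Make baseline-adjusted ANCOVA of ZBS at T2 the primary analysis. State the correlation that the sample size relies on (about 0.67 for 80 completers per group) and show power over r = 0.5 to 0.8. The value 0.67 is back-solved from 80, so the correlation should be supported by the original calculation or by outside data.
- **(b)** State that 80 analysed per group gives about 55% power for 0.33 SD, or 80% power for about 0.45 SD.

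In either case, say that 104 per group tolerates 23% dropout, and give the power at 30% dropout (about 51% unadjusted).

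Cost: no extra participants or assessments, since Table 1 already schedules ZBS at T0 and T2. Option (b) is wording only, with a less favourable power statement. Option (a) also fixes the primary analysis, so it should be settled before outcome data are examined by arm.

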### Statistical analyses

Analyses will be conducted according to the intention-to-treat principle. Randomization efficacy will be assessed by examining characteristics in the iSupport condition compared to EOC and missing data and unbalance will be evaluated. Missing data on follow-up measurements will be imputed using multiple imputations. To examine the association between the experimental and comparison group on the primary and secondary outcomes, we will first calculate paired *t* tests and estimates of effect sizes will be calculated. By using multiple regression analyses, we can correct for possible confounders. With a “generalized estimating equations” (GEE) analysis the research question regarding the maintenance of the effectiveness of the intervention will be answered for primary and secondary outcomes in separate models [41]. Thus, all primary and secondary outcome measures will be analyzed using separate GEE models using each separate outcome measure as the dependent variable and an indicator for the intervention (the iSupport intervention compared to the education-only control) as the primary independent variable. Potential confounders will be added to these models. All analyses will be conducted using SPSS for Windows.

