There are some factors that may hinder participant inclusion for the trial. Firstly, online self-help training and the support program for caregivers are not commonly used and may not yet be readily accepted, particularly not by older caregivers in India. In general, receiving health information via the Internet in India is still relatively new. This may hamper the recruitment because caregivers tend not to automatically search for help on the Internet in general, which might also be exacerbated by the stigma related to dementia and to help-seeking [44]. This may also result in a relatively high dropout rate during the intervention period. Moreover, participants in the study may be younger (adult children) caregivers who are more familiar with the Internet as compared to older (spousal) caregivers. Another challenge is that the program is in English, and although many Indian people speak English, there is a low literacy rate (69.3% in 2011) [45] and it is certainly not the only language spoken in this country. This will result in the inclusion of a subgroup of caregivers that is highly educated [15, 46]. Another challenge may be that some households may not have reliable Internet coverage. Although this problem may decrease over time as the World Bank projects the greatest increases in Internet coverage to be in lower-middle income countries over the next few years, it may result in dropout during the study [47].

Anticipating challenges for inclusion and dropout, this study can be viewed as a first attempt to show the feasibility and potential of a self-help Internet-based training and support program for caregivers of people with dementia in a lower-resourced setting. A scalable approach is needed, given the large population of (adult child) caregivers of people with dementia, the urgent need for skills training and support to prevent and reduce caregiver distress, the growing number of Internet users, as well as the relatively low cost of such interventions [16, 18]. This also holds for other mental health interventions to reduce the mental health treatment gap [34, 48]. Internet-based interventions like iSupport may have potential for adaptation in differently resourced settings, and may help people with mental health problems around the world (Additional file 1).

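### The 30% dropout allowance keeps the required 80 per group only up to 23% loss; at 30% loss about 73 would remain

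*Protocol article*

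**What the plan says.** The section Sample size calculation in the protocol article sizes the trial on change in the Zarit Burden Scale six months after baseline, with two-sided alpha 0.05 and 80% power. It reports that the "minimum sample size for each group was identified as 80". The allowance for attrition follows in one sentence: "To take account of study dropout we increase this number by 30% (*N* = 208; 104 per group".

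This 30% is the only number tied to dropout anywhere in the article. The Discussion speaks of dropout in words only. It says of the low familiarity with online health help: "This may also result in a relatively high dropout rate during the intervention period". It adds unreliable Internet coverage as a further cause.

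The section Statistical analyses handles losses as follows: "Missing data on follow-up measurements will be imputed using multiple imputations". Table 1 schedules the burden scale at T0 and T2 only. At T1 it schedules the CES-D10, the EQ-5D and the mastery scale.

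**The concern.** An allowance for dropout should let the required number survive the expected loss. Loss is a fraction of those randomised, so the number to randomise is the required number divided by the fraction retained. Adding a percentage to the required number gives a smaller figure, and the gap widens as the percentage grows.

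A reader who sees 30% named as the provision for dropout will naturally take 30% attrition to be covered. It is not. The loss actually covered is 23%. Since the Discussion expects dropout to be relatively high, the true tolerance is a figure the team needs. Trial status says enrolment is under way, so it can still be used.

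**Working it through.** **Inputs**, all from Sample size calculation unless noted:

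- Required number per group: 80.
- Increase for dropout: 30%.
- Number to randomise: 104 per group, 208 in total.
- Allocation: equal (Randomization).
- Expected dropout rate: not stated anywhere.

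**Step 1. Reproduce the plan's figure.** 80 × 1.30 = 104 per group, and 2 × 104 = 208. This matches exactly. Division by the retained share, 80/(1 − 0.30) = 114.3, does not match, so the plan multiplied.

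**Step 2. Loss that 104 per group tolerates.** The margin is 104 − 80 = 24 per group, and 24/104 = 23.1%. The retained share must therefore be at least 80/104 = 76.9%.

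This does not depend on the base of 80. Any required number multiplied by 1.30 tolerates a loss of 0.30/1.30 = 23.1%.

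**Step 3. Other loss rates.** Remaining = 104 × (1 − d). Needed to keep 80 = 80/(1 − d), rounded up. The rates d are illustrations, since the article gives none.

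| Loss by T2 (assumed) | Remaining of 104 per group | Needed per group to keep 80 |
|---|---|---|
| 20% | 83.2 | 100 |
| 23% | 80.1 | 104 |
| 25% | 78.0 | 107 |
| 30% | 72.8 | 115 |

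At 30% the shortfall is 80 − 72.8 = 7.2 per group, about 14 in total. Covering it would take 115 − 104 = 11 more randomised per group, or 22 more in total (N = 230).

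**Step 4. Does imputation close the gap?** Not in general. No burden score is scheduled between T0 and T2, so a missing T2 score has no interim burden value to inform it. The CES-D10, EQ-5D and mastery scores at T1 can help for caregivers who complete T1 and are lost afterwards. How much they help cannot be computed from the article.

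**Step 5. Why no power loss is quoted.** The plan gives this effect: "A standardized effect size of .33". At 0.33, with two-sided 0.05 and 80% power, a plain two-group comparison needs 145 per group by the normal formula (146 by t test), and 80 per group has about 55% power. Reaching 80% power with 80 per group would need an unstated baseline correlation: about 0.67 with baseline adjustment, or about 0.72 with change scores if 0.33 is scaled by the cross-sectional SD. A power figure for 73 per group would therefore rest on an effect or a correlation that the article does not state.

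**The case against.** The strongest reply is that the text contains no arithmetic error. It says the number is increased by 30%, and 80 increased by 30% is 104. It does not say that 30% of caregivers are expected to drop out. Read literally, it provides 24 extra caregivers per group, which is coherent and covers losses up to 23%. This stands. A reader might infer that the required size and the allowance contradict each other, or that the plan ought to have divided by 0.70. Both follow only once a 30% dropout rate is supplied, and the article does not supply one.

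Three other stronger readings also fail:

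- A reader might suppose that the team is monitoring against a 70% retention target. The article sets no retention target.
- A reader might argue that a missing T2 burden score can be recovered only from baseline. The scales scheduled at T1 say otherwise.
- A reader might say that power falls from 80% to about 76% at 30% loss. That calculation holds only if 80 per group gives 80% power, which implies an effect of about 0.446 SD, not the 0.33 in the plan.

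It is also fair to say that the base of 80 is the larger question in the same section. That does not remove this point: if the base is revised and still multiplied by 1.30, the tolerance stays at 23%.

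**Conclusion.** The point holds as a minor one. That 104 per group retains 80 only up to 23.1% loss needs nothing beyond the plan's own two numbers. That about 73 per group remain, against a required 80, rests on the assumption that 30% was meant as the dropout rate. This is the natural reading, because the figure is introduced for dropout and no other is given, but the wording does not prove it. On that reading the shortfall is about 7 caregivers per group. If actual loss stays within 23%, there is none.

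On either reading the article leaves the tolerated loss unstated, and the one percentage it offers is higher than the loss covered. Nothing here shows that the randomisation, the planned analyses or N = 208 must change.

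**What to change.** Keep N = 208 and restate the allowance in Sample size calculation, for example:

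> 104 per group are randomised. This retains the required 80 per group if dropout at T2 is no more than 23%; at 30% dropout about 73 per group remain.

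If a dropout rate was expected when the trial was sized, state it. Aim for a T2 burden score from at least 77% of those randomised in each group (104 × 0.77 = 80.1). In any re-sizing, compute the number to randomise as n/(1 − dropout).

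Do not add a power figure for 73 per group until the derivation of the 80 has been explained.

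The cost is a corrected sentence and a retention aim, with no extra participants. The downside is a slightly less favourable stated tolerance for dropout.

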### Outcomes

The primary outcomes are burden and symptoms of depression and anxiety (Table 1). Burden is measured by the 22-item Zarit Burden Scale [35]. Responses range from 0 (never) to 4 (nearly always). Depressive symptoms are measured using the modified version of the Center for Epidemiological Studies Depression scale (CES-D10): ten items measuring frequency of common depressive symptoms (e.g., sadness, hopelessness, sleep and appetite disturbances) in the past week. Response categories are: 0 (rarely or none of the time present) to 3 (most or all of the time present) [32]. Anxiety symptoms are measured using the General Anxiety Disorders scale (GAD-7), a 7-item measure rating the frequency of common anxiety symptoms (nervousness, worry, not being able to relax, being restless, annoyed or irritable, and feeling afraid that something awful will happen) in the past 2 weeks. Response categories are: 0 (not at all), 1 (several days), 2 (more than half the days) and 3 (nearly every day) [30].

**Table 1 Tab1:** Primary and secondary outcome measures and study variables in the iSupport online support trial

Outcome measures in the randomized controlled trial (RCT) (number of items, response scale, total scale score range)						
Primary	Target of scale	Reliability and validity of scales	Cronbach’s alpha	Pre measurement (T0)	First Follow up (T1)	Second Follow-up (T2)
Zarit Burden Scale (22, 0–4, 0–88)^a^	Perceived stress of caregiving	Intra-class correlation coefficient (ICC): 0.88 to 0.89	Cronbach’s α = 0.82 to 0.93	X		X
CES-D10 Center for Epidemiological Studies Depression Scale (10 items, 0–3, 0–30)^b^	Depression	Test-retest reliability (r values = 0.41 to 0.70)	Cronbach’s α = 0.80 to 0.85	X	X	X
GAD Generalized Anxiety Disorder 7-item scale (7 items,0–3, 0–21)^c^	Anxiety	ICC = 0.83	Cronbach’s α = 0.92	X		X
Secondary						
EuroQoL-5D Descriptive system of health-related quality of life states consisting of 5 dimensions (mobility, self-care, usual activities, pain/discomfort, anxiety/depression).^d^	Quality of Life	ICC = 0.70	No overall Cronbach's α reported		X	X
Mastery (7 items, 1–4, 7–28)^e^	Perlin 7-item Mastery Scale	Principal component factor loadings ranging from − 0.47 to 0.76			X	X
Self-efficacy (1, 0–5, 0–40)^f^	RIS Self-efficacy Scale	*r* = 0.48 to 0.69	Cronbach’s α = 0.72 to 0.79			X
Confounders/modifying Variables						
Behavioral Problems RMBPC (6, 0–4, 0–24)^g^	Revised Memory and Behavioral Problems Checklist	Rs = 0.29, .31, .26; ps < .01 correlations between subscales and caregiver depression (CES-D) and burden (Caregiver Stress Scale)	Cronbach’s α values are: .75 for frequency and .76 for reaction for memory problems .82 and .77 for depression and .62 and .70 for disruptive behavior	X		X
Functional status of person with dementia AD^h^	Informant Questionnaire on Cognitive Decline in older people (AD8)	*r* = 0.75	Cronbach’s α = 0.84	X		X
Demographic variables caregiver’s age, caregiver sex, relationship to the person with dementia (spouse, adult child, or other family member), level of education, living arrangement (living together or apart from the person with dementia)				X		

^a^Zarit S, Reever KE, Back Peterson. Relatives of the impaired elderly: correlates of feelings of burden. The Gerontologist. 1980;20:649–655

^b^Björgvinsson T, Kertz SJ, Bigda-Peyton JS, McCoy KL, Aderka IM. Psychometric properties of the CES-D 10 in a psychiatric sample. Assessment*.* 2013;20: 429–436

Radloff LS. CES-D scale: a self report depression scale for research in the general populations. Applied Psychological Measurement*.* 1977;1:385–401

^c^Spitzer R, Kroenke K, Williams JBW, Lowe B. A brief measure for assessing generalized anxiety disorder. Arch Inern Med*.* 2006;166:1092–1097

^d^Brooks R, Rabin R, de Charro F (Ed.). The measurement and valuation of health status using EQ-5D: a European perspective: evidence from the EuroQol BIO MED Research Programme. Rotterdam: Kluwer Academic Publishers; 2003

^e^Pearlin LI, Schooler C. The structure of coping. Journal of Health and Social Behavior*.* 1978;19:2–21

^f^Steffen A, McKibbin C, Zeiss A, Gallagher-Thompson D, Bandura A. Revised Scale for Caregiving Self-Efficacy: reliability and validity studies. J Gerontol B Psychol Sci Soc Sci*.* 2002;57: P74–P86

^g^Teri L, Truax P, Logsdon R, Uomoto J, Zarit S, Vitaliano PP. (1992). Assessment of behavioral problems in dementia: The Revised Memory and Behavior Problems Checklist (RMBPC*).* Psychology and Aging*.* 7(4):622–31.

^h^Galvin JE, Roe CM, Powlishta KK, Coats MA, Muich SJ, Grant E, Miller JP, Storandt M, Morris JC. The AD8: a brief informant interview to detect dementia. Neurology. 2005; 65:559–564

^h^Galvian JE, Roe CM, Xiong C, Morris JC. Validity and reliability of the AD8 informant interview in dementia. Neurology. 2006;67:1942–1948

The secondary outcomes are caregiver quality of life, person-centered attitude, self-efficacy and mastery. Quality of life is measured by the EuroQol-5 Dimension (EQ-5D) [37]. Person-centered attitude is measured by a subscale within the Approaches to Dementia Questionnaire (ADQ) [38]. For measuring self-efficacy we use the RIS Eldercare Self-efficacy Scale [39]. Mastery is measured using the 7-item Pearlin Mastery Scale [40].

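### The protocol is inconsistent about which outcome decides the trial: the objective omits burden, the sample size rests on burden, and three unranked primaries have no success rule

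*Protocol article*

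**What the plan says.** Statements in the protocol article that bear on which outcome decides the trial:

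- **Objective (Methods and analyses):** "The objective is to examine the effect of this online self-help training and support program on depression and anxiety outcomes". Burden is not mentioned.
- **Sample size calculation:** "Sample size calculation is guided by the primary outcome change in burden (ZBS) at 6 months after baseline". The outcome is named in the singular. The standardized effect is 0.33, at two-sided alpha 0.05 and 80% power. This is the only significance level in the article.
- **Outcomes and Table 1:** "The primary outcomes are burden and symptoms of depression and anxiety (Table 1". The Abstract and the Discussion list the same three. None of these places ranks them.
- **Statistical analyses:** "all primary and secondary outcome measures will be analyzed using separate GEE models". No significance level, order of testing or success criterion is given.

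**The concern.** A reader cannot tell from this document which result makes the trial positive. The outcome that fixed the number of participants is absent from the objective. The two outcomes in the objective have no power statement. The outcome list puts all three on an equal footing.

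If this stays open until results are known, the choice of deciding outcome can follow the data. One significant scale out of three could then be reported as a positive primary result, and the false-positive rate of that claim would exceed the 5% used to size the trial. The opposite reading, that all three must succeed, carries no such inflation but has less power than the calculation for burden implies. The document supports neither reading over the other.

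**Working it through.** **1. The statements side by side**

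| Place | Outcomes named | Alpha or power given |
|---|---|---|
| Methods and analyses (objective) | depression, anxiety | none |
| Sample size calculation | burden (ZBS), 6 months | two-sided 0.05, 80% |
| Abstract, Outcomes, Table 1, Discussion | burden, depression, anxiety | none |
| Statistical analyses | every outcome, separate models | none |

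The second and third rows can coexist, because a trial may be sized on one of several primaries. The first row fits neither: it drops the outcome that the second relies on and that the third lists first.

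**2. The plan's own figure**

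For a plain comparison of two means, n per group = 2[(z₀.₉₇₅ + z₀.₈₀)/d]² = 2[(1.960 + 0.842)/0.33]² ≈ 144.1, so 145. The article states 80, which does not reproduce from its stated inputs. It would need an unstated gain, such as a correlation between baseline and follow-up of about 0.67 under covariance adjustment. That is a separate matter, and nothing in steps 3 and 4 uses the 80.

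**3. Family-wise error if any one of three counts**

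Two assumptions are needed. Each primary is tested at two-sided 0.05 (stated only for burden), and any one significant result counts as success (stated nowhere).

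Independent tests: 1 − (1 − 0.05)³ = 1 − 0.857 = 0.143.

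For a common correlation ρ between the test statistics, with c = 1.960:

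1 − ∫ φ(u) [Φ((c − √ρ·u)/√(1−ρ)) − Φ((−c − √ρ·u)/√(1−ρ))]³ du

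| Assumed ρ | Chance of at least one false positive |
|---|---|
| 0 | 14.3% |
| 0.3 | 13.6% |
| 0.5 | 12.5% |
| 0.7 | 10.9% |
| 0.9 | 8.4% |

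The article gives no correlations between the three scales, so ρ is an assumption and the range is the result.

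**4. Power if three primaries are kept with error control**

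Holm compares the smallest p-value with 0.05/3 = 0.0167, the next with 0.025 and the last with 0.05. At the strictest step z = 2.394. Take an outcome whose n gives exactly 80% power at 0.05. Its power at 0.0167 is Φ(1.960 + 0.842 − 2.394) = Φ(0.408) ≈ 0.66.

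If burden alone is primary, or is tested first in a fixed order, its alpha stays 0.05 and its power does not change.

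**The case against.** The strongest reply is that this is a condensed article. Allocation of alpha and order of testing commonly sit in the statistical analysis plan, which is not shown. That stands as far as it goes: the absence of a named multiplicity method is not, by itself, a fault here. But the conflict between the objective and the sample size is on the page, and an analysis plan could settle it only by overriding one of those sections.

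Several stronger readings are tempting, and the document does not support them:

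- **That the plan tests each primary at 0.05 and accepts any one.** This is an inference. The 0.05 belongs to the burden calculation, and no success rule is written. If all three had to succeed, error would not inflate.
- **That three sections give three rival definitions of the primary.** The Abstract, Outcomes and Discussion agree with each other, and sizing on one listed primary is ordinary practice. The objective never uses the word primary. The clear conflict is its omission of burden.
- **That measuring CES-D10 at T1 adds another primary test.** Table 1 shows an additional measurement. The analysis section describes one model per outcome and no separate confirmatory test at T1.
- **That error control would explain a large shortfall against 80 per group.** Bonferroni alone multiplies n by [(2.394 + 0.842)/(1.960 + 0.842)]² ≈ 1.33. The plain formula already gives 145 at alpha 0.05, so most of any such gap is the separate sample-size question.

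It can also be said that the Discussion presents the study as an early look at feasibility and potential. That lessens the weight of strict family-wise control. It does not remove the need to say which result decides, because the design section says the trial is meant to establish effectiveness.

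**Conclusion.** The point holds as an inconsistency with a missing decision rule. The objective names two outcomes without burden, the sample size rests on burden, and three unranked primaries are analysed separately with nothing to say what counts as success.

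The consequence is conditional. If each primary is tested at 0.05 and any one suffices, the chance of at least one false-positive primary is between about 8% and 14% over the assumed correlations from 0.9 down to 0. It falls to 5% only if the tests are perfectly correlated. The textual conflict needs none of these assumptions.

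**What to change.** Rewrite the objective to include burden, and state the decision rule before outcome data are seen. The Trial status section reports that enrolment is under way, so this should be done now. Two options would work:

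1. **Single primary.** Make ZBS at T2 (6 months), the outcome the trial was sized for, the only primary at two-sided 0.05. Make CES-D10 and GAD-7 at T2 key secondary outcomes, tested at 0.05 in a fixed order and only after a significant ZBS result, each depending on the one before. The investigators should choose the order of the two, since the article gives no basis for one.
2. **Three primaries.** Keep all three, apply Holm across the three T2 contrasts, and restate the power.

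Either option means aligning the wording of the objective, outcomes, sample size and analysis sections, and the registry entry where it differs. No added enrolment is proposed.

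Under option 1, claims about depression and anxiety become conditional on burden. That cost is real: at d = 0.33, without a gain from baseline correlation, power for burden is about 55% with 80 per group and 66% with 104, so the later tests would often not be reached. Under option 2, an outcome with nominal 80% power has about 66% at the strictest step.
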